### 2.6. HRTP Therapy (Intervention)

As mentioned above, the HRTP is a novel approach for the treatment of racial trauma, with roots in CBT, FAP, and ACT (Williams, 2024). The said protocol consists of 12 sessions, each 60 min in length, spanning three stages: (1) Stop the Bleeding–Stabilization and Support; (2) Healing the Wounds of Racism; and (3) Empowerment. Within phase 1 or “Stabilization”, therapists support their clients in understanding the wide-reaching effects of racism as well as racism’s relationship to racial trauma and other related conditions. As such, these early sessions are rich in psychoeducation and the thoughtful validation of each client’s experiences of racism and their reaction to these events. The therapist also helps the client make use of functional coping strategies against racism, with attempts made to increase the client’s self-care practices and enlarge their social support network.

Within phase 2 or “Healing”, the therapist moves towards processing the client’s upsetting experiences of racism. To start, the therapist guides the client in exploring and dismantling any internalized racism, offering genuine affirmations to expedite the process. The topic of colorism is also explored in great depth, and steps are taken to strengthen the client’s ethnoracial identity via psychoeducation and cultural engagement. Following this, two sessions are dedicated to having therapists bear witness as clients recount and habituate to racism-related traumatic experiences via imaginal exposures and/or other creative means (e.g., written expression and photovoice). To facilitate processing, therapists validate and reflect back client experiences, identify any negative cognitions about the client’s self-view that are reinforced by the traumatic experience, and offer a possible counternarrative. Finally, the therapists introduce microinterventions, role-playing, and imagery rescripting as tools to combat racism in various scenarios.

In phase 3 or “Empowerment”, the therapist supports clients in positively transforming their values, actions, and relationships in the wake of their past traumatic experiences (i.e., achieving posttraumatic growth). The therapists will also help their clients explore what their experiences mean to them (i.e., meaning-making). The final sessions of the HRTP consider how participating in social action and activism can also lead to continued healing. A last session will be used to review key concepts, celebrate gains, and discuss a plan to maintain wellness in the face of continued racism post therapy.

### 2.7. Treatment as Usual (Control)

Given the lack of validated alternative treatments for the healing of racial trauma (Williams et al., 2021), a TAU control group will be used. As such, participants will be referred to treatment at the authors’ host institution’s community mental health clinic after the completion of the intake assessment. The said clinic employs a variety of evidence-based therapeutic approaches, including CBT, emotionally focused therapy, existential therapy, interpersonal therapy, and psychodynamic therapy. Participants within the TAU group will receive 12 sessions of one of the said therapies (supervisor dependent).

### 2.8. Study Measures

The study measures included in the trial are two intake measures, three primary outcome measures, and two secondary outcome measures. Before study admission, two intake measures will be administered to prospective participants. These measures will be used to assess if prospective participants meet the study’s inclusion criteria and to better understand the participants’ mental health profiles.

The *Mini International Neuropsychiatric Interview* (MINI 7.0.2; Sheehan et al., 1998) is a semi-structured diagnostic interview designed to briefly assess 17 of the most common mental disorders according to the *Diagnostic and Statistical Manual of Mental Disorders, Fifth Edition* (DSM-5) criteria. The modules assessed include major depressive episodes, suicidality, manic and hypomanic episodes, panic disorder, agoraphobia, social phobia, obsessive–compulsive disorder, post-traumatic stress disorder, alcohol use disorder, substance use disorder, psychotic disorders and mood disorders with psychotic features, anorexia nervosa, bulimia nervosa, binge eating disorder, and generalized anxiety disorder, among others. The MINI was initially created for cross-cultural application and has since been adapted for use in several languages and diverse populations worldwide (e.g., Churbaji et al., 2020; Eytan et al., 2007).

The *University of Connecticut Racial/Ethnic Stress & Trauma Survey* (UnRESTS; Williams et al., 2018a) is a semi-structured diagnostic interview for assessing racial trauma. It consists of several parts, including probes around an individual’s racial and ethnic identity development, experiences of direct overt racism, experiences of racism by loved ones, experiences of vicarious racism, and experiences of covert racism (or microaggressions). The interview concludes with a 29-item checklist which assesses whether an individual’s racial trauma satisfies a DSM-5 diagnosis for PTSD. To render a racial trauma diagnosis (Williams & Zare, 2022), an individual must satisfy the criteria for a minimum of three of the four PTSD symptom clusters as per the checklist (i.e., re-experiencing, avoidance, negative changes in cognition and mood, and physiological arousal and reactivity). The said symptoms must also be clinically significant and must have been present for a month or more.

### 2.9. Primary Outcomes

Three primary outcomes will be measured at five time points for the treatment group (weeks 0, 4, 8, 12, and 28) and twice for the TAU control group (weeks 0 and 12). See Table 1 for the participants’ assessment schedule. Of note, there will be a differential assessment schedule for TAU versus HRTP participants. That is, HRTP participants are assessed on three more occasions than those in the TAU group. Two of these additional assessment periods are included within the intervention arm’s active treatment phase (weeks 4 and 8) to better understand how each HRTP phase impacts healing/racial trauma symptom severity. Week 4 roughly translates to the participants transitioning to the Healing phase and week 8 the Empowerment phase. Further, those in the control arm have no need for a post-treatment follow-up as upon receiving TAU, they may be immediately enrolled within the treatment group to receive the HRTP.

The *Racial Trauma Scale* (RTS; Williams et al., 2022c) is a 30-item clinical measure which examines the severity of traumatic symptoms due to racism. More specifically, the RTS asks individuals to “think about all the times when you have heard about, seen, or experienced racial discrimination” and how much they have been bothered by resultant thoughts, behaviours, or symptoms on a 4-point scale (where 1 is “not at all” and 4 is “extremely”). Of note, within this study specifically, when completing the RTS, clients will be asked to rate symptoms as per their lived experience over the previous month/30 days. An RTS total score is calculated by summing all item ratings together. Moreover, subfactors of the RTS include “Lack of Safety”, “Negative Cognitions”, and “Difficulty Coping”. Higher RTS total and subfactor scores indicate greater symptom distress. In consideration of the RTS’s convergent validity, RTS responses were found to be highly correlated with several measures of trauma, including the *PTSD Checklist for the DSM-5* (PCL-5; r = 0.79) and the *General Ethnic Discrimination Scale* (r = 0.76). The RTS was developed for and tested with diverse ethnoracial populations. The RTS also has excellent reliability (α = 0.97; Williams et al., 2022c).

The *Beck Depression Inventory* (BDI-II; Beck et al., 1996) is a 21-item clinical measure used to evaluate the severity of depressive symptoms in populations aged 13+. In so doing, respondents are asked to consider 21 groups of statements and choose the statement that most aligns with their experience over the previous 2-week period. Each item’s statements exist on a scale running from 0 to 3. For example, on the item of “self-criticalness” respondents select from the following group of related statements “0—I don’t criticize or blame myself more than usual; 1—I am more critical of myself than I used to be; 2—I criticize myself for all of my faults; 3—I blame myself for everything bad that happens”. A total score is then calculated by summing up all items’ corresponding statement ratings, with higher scores suggestive of a greater severity of depressive symptoms. Total BDI–II scores within the 0–13 range are indicative of no or minimal depression, 14–19 mild depression, 20–28 moderate depression, and 29–63 severe depression. The test–retest reliability of the BDI-II is between 0.73 and 0.96 (Wang & Gorenstein, 2013). Moreover, convergent validity was tested against several validated measures of depression, with correlation coefficients ranging from 0.57 to 0.94. Also, Sashidharan et al. (2012) found no evidence of racial bias in the BDI-II.

Finally, the *Trauma Symptoms of Discrimination Scale* (TSDS; Williams et al., 2018b) is a two-part clinical measure of discriminatory distress. In the first part, which is 21 items, individuals characterize the severity of anxiety-related trauma symptoms including avoidance, negative cognitions, social fears, and worries about the future. Items are rated on a 4-point scale (where 1 is “never” and 4 is “often”), and higher TSDS scores indicate greater distress caused by discriminatory acts. Of note, within this study specifically, when completing the TSDS, clients will be asked to rate distress as per their lived experience over the previous month/30 days. In the TSDS’ second part, individuals are asked to select what form of discrimination they have experienced, including racial/ethnic, gender, sexual orientation, religion, age, and/or other types of discrimination. Moreover, individuals can check multiple forms of discrimination. The TSDS was tested against several known measures of psychopathology and experiences of racism, including PTSD symptoms (PCL-5; *r* = 0.69), traumatic cognitions (*Post Traumatic Cognitions Inventory*; *r* = 0.65) and racial trauma (*Race-Based Traumatic Stress Symptom Scale—Short Form*; *r* = 0.69). The TSDS was developed for and tested with diverse ethnoracial groups (Williams et al., 2023b).

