### 2.12. Statistical Analysis

Descriptive statistics, including means, standard deviations, and frequencies, will be calculated for continuous primary and secondary outcomes. Differences in primary and secondary outcomes, including TSDS, RTS, change in symptoms, and therapeutic experiences, will be examined using a two-way mixed ANOVA with two or three within-subject levels of time (pre-test, post-test, and follow-up) and two between-subject levels of condition (HRTP and control). When there is evidence of sphericity violation, we will use the Greenhouse–Geisser correction (Greenhouse & Geisser, 1959). It is predicted that participants’ TSDS and RTS scores will decrease significantly over the course of the treatment. It is also predicted that TSDS and RTS scores at follow-up will be the same or lower than at the end of the treatment.

Both the short-term and long-term efficacy of the HRTP will be examined during the treatment (week 0, 4, 8), at the end of the treatment (week 12), and 4 months after the treatment (week 28). Assessment will take place at four time points for the treatment group (HRTP therapy; weeks 0, 4, 8, 12, and 28; see Table 1 for participants’ assessment schedule) and only two time points for the control TAU group (T0 and T4; see Table 1 for participants’ assessment schedule). Analysis will compare standard mean differences (SMDs) between the time points for the treatment group (weeks 0, 12, and 28) and the control group (weeks 0 and 12). Analyses will entail intent to treat (ITT) and include participants with pre-treatment and the last time point available as long as they attended at least one treatment session. We examine significant levels for the analysis as well as effect sizes. A significance level of *p* < 0.05 will be used for all tests.

For each outcome of interest, we will identify any significant Condition × Time interactions. When no interaction is found, significant main effects will be reported. Partial eta-squared (η2) was used to measure effect sizes for the ANOVAs. When significant interactions are found, post hoc tests of simple main effects will be used to examine the differences, *p* values will be included for all post hoc tests, and 95% confidence intervals (CIs) will be used for all *p* values less than 0.05. Additionally, we will conduct comparisons of baseline data for completers and non-completers. Subgroup analysis will be based on age, gender, and levels of racial stress and trauma.

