The secondary outcomes will compare the quality of the therapeutic experiences throughout the treatment group (HRTP therapy; weeks 4, 8, 12), as well as comparing the quality of the sessions between the treatment and control groups (week 12). The strength of the therapeutic alliance between the participants and therapists (Helping Alliance Questionnaire; Luborsky et al., 1996) will be evaluated, as will whether or not the participants perceived any microaggressions in their sessions (Racial Microaggressions in Counselling Scale; Constantine, 2007).

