## Figures and Tables

**Figure 1 behavsci-15-00856-f001:**
[figure not shown]
Participant flow diagram in HRTP Trial.

**Table 1 behavsci-15-00856-t001:** Participant assessment schedule.

Time	Session	Week	Measures	
			Intervention Group	Control/TAU Group
T1	Intake	0	MINI; UnRESTS; BDI-II; RTS; TSDS	
T2	4	4	BDI-II; RTS; TSDS; HAq-II; RMCS	nothing
T3	8	8	BDI-II; RTS; TSDS; HAq-II; RMCS	nothing
T4	12	12	BDI-II; RTS; TSDS; HAq-II; RMCS	BDI-II; RTS; TSDS; HAq-II; RMCS
T5	Follow Up	28	BDI-II; RTS; TSDS	participants will have withdrawn from the study or started the protocol

Note. BDI-II: Beck Depression Inventory-II; HAq-II: Helping Alliance Questionnaire-II; MINI: The Mini International Neuropsychiatric Interview; RMCS: Racial Microaggressions in Counselling Scale; RTS: Racial Trauma Scale; TSDS: Trauma Symptoms of Discrimination Scale; UnRESTS: University of Connecticut Racial/Ethnic Stress & Trauma Scale.

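### At week 12, the only post-baseline time measured in both arms, HRTP participants complete the primary scales for the fourth time and TAU participants for the second, so any additional effect of the two extra completions is confounded with treatment

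*Protocol article*

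**What the plan says.** Section 2.9 has the three primary outcomes "measured at five time points for the treatment group (weeks 0, 4, 8, 12, and 28"). In the comparator arm, by contrast, the same scales are scheduled "twice for the TAU control group (weeks 0 and 12"). It calls the schedule differential and notes that "HRTP participants are assessed on three more occasions than those in the TAU group". Its reason for the two mid-treatment assessments is that they fall in the intervention arm's "active treatment phase (weeks 4 and 8) to better understand how each HRTP phase impacts healing/racial trauma symptom severity". The missing TAU follow-up is explained by TAU participants being able to move on to HRTP.

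Table 1 agrees. The TAU cells at weeks 4 and 8 read 'nothing', and at week 28 the TAU entry is "participants will have withdrawn from the study or started the protocol".

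Section 2.12 repeats that there are "only two time points for the control TAU group" and compares standardised mean differences "between the time points for the treatment group (weeks 0, 12, and 28) and the control group (weeks 0 and 12"). It keeps in the analysis anyone with a pre-treatment score who attended at least one session, using the last time point available. For the therapist-rating scales it also plans on "comparing the quality of the sessions between the treatment and control groups (week 12").

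**The concern.** RTS, TSDS and BDI-II are all rated by the participant. Filling in such a scale repeatedly can change later answers through familiarity, self-monitoring or added contact with the study. When both arms follow the same schedule, this affects both and drops out of the comparison. Here the number of earlier completions is fixed by arm. Randomisation cannot balance it, because it arises after allocation and comes with the allocation.

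The stake is the week-12 contrast between arms. TAU has no later measurement, so this is the only randomised post-baseline comparison in the trial. A measurement difference there enters the treatment estimate directly, and data never collected from TAU cannot be recovered at the analysis stage.

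**Working it through.** **1. Count of completions** (section 2.9, Table 1)

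| | Weeks | Total | Up to and including week 12 |
|---|---|---|---|
| HRTP | 0, 4, 8, 12, 28 | 5 | 4 |
| TAU | 0, 12 | 2 | 2 |
| Difference | | 3 | 2 |

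The plan's own figure of three more occasions is reproduced: 5 − 2 = 3. Two of the three fall before the week-12 comparison and one (week 28) after it. Section 2.12 speaks of four time points for HRTP but lists five weeks; section 2.9 and Table 1 support five.

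**2. Shared post-baseline times.** The weeks common to both arms are 0 and 12, so week 12 is the only shared post-baseline time. Section 2.4 mentions a 4-month follow-up before TAU participants are offered HRTP, but sections 2.9 and 2.12 and Table 1 schedule no TAU measurement then.

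**3. What cancels and what does not.** Write r2 for the score change caused by a second completion, and r4 for the change caused by having reached a fourth. Then:

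- observed week-12 difference = treatment effect + (r4 − r2)

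The part common to both arms cancels. Only the additional effect b = r4 − r2 remains. The documents give no value for b, and it may be negative, zero or positive.

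**4. Sensitivity illustration (b is assumed).** Inputs from section 2.2: 48 per group, 20% attrition, two-sided alpha 5%, hypothesised SMD 0.36 to 0.52.

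- Evaluable per arm: 48 × 0.80 = 38.4, taken as 38; df = 2 × 38 − 2 = 74; critical t = 1.993.
- Non-centrality = |b| × √(38/2) = |b| × 4.359.
- No true treatment effect; independent-samples t-test, as named in section 2.2.

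| Assumed \|b\| (SD) | Non-centrality | Chance of a significant result in the direction of b | Share of SMD 0.52 | Share of SMD 0.36 |
|---|---|---|---|---|
| 0 | 0 | 2.5% | 0% | 0% |
| 0.05 | 0.218 | 4.1% | 10% | 14% |
| 0.10 | 0.436 | 6.3% | 19% | 28% |
| 0.20 | 0.872 | 13.6% | 38% | 56% |

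The table is symmetric. If repeated rating lowers HRTP scores, the false result favours HRTP; if it raises them, the false result goes against HRTP.

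**5. Dropouts.** Under the last-available rule in section 2.12, an HRTP participant who leaves before week 12 can contribute a week-4 or week-8 score. A TAU participant who leaves before week 12 has only the baseline score, so contributes either no change or nothing. With 20% attrition planned, the rule works on different material in the two arms.

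**6. Therapist-rating scales.** By Table 1, HRTP participants complete HAq-II and RMCS at weeks 4, 8 and 12, and TAU participants at week 12 only. At week 12 that is a third completion against a first. Section 2.10, however, says these scales are measured in the treatment group alone, which conflicts with Table 1 and with the between-group comparison in section 2.12.

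**The case against.** The authors disclose the unequal schedule and give a reason for it: they want to see how symptoms move across the phases of HRTP. Both arms receive 12 sessions, so two questionnaire packs four weeks apart may add little to the contact that everyone has. The documents offer no evidence that repeated completion of these scales shifts scores at all.

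Most of this stands as a limit on size. The disclosed reason explains why HRTP is measured at weeks 4 and 8; it does not explain why TAU is not. The crossover reason concerns only follow-up after treatment.

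A reader might go further and infer three things that the documents do not support:

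- **That every retest drop is counted as HRTP benefit.** Both arms go from a first to a second completion, and that change cancels. Only the additional effect of the two extra completions is at issue.
- **That the bias favours HRTP.** No direction is given. The RTS asks respondents to bring to mind all their experiences of discrimination, and repeating that request could raise reported distress as easily as familiarity could lower it.
- **That the percentages estimate the trial's false-positive rate.** They rest on an assumed artefact, no true effect and a simple t-test. Section 2.12 also plans a mixed ANOVA, for which the rates would depend on the pre-post correlation and could be higher or lower.

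**Conclusion.** The concern holds in a limited form. The schedule ties two extra completions of self-report primary scales to the HRTP arm before the only randomised post-baseline comparison, and no analysis can separate their additional effect from treatment. The counts (four against two) are certain. The sign and size of the effect are unknown, and zero is possible. The movement from 2.5% to 13.6% rests on an assumed artefact of up to 0.20 SD in either direction, 38 evaluable per arm and no true effect; it shows sensitivity, not a demonstrated bias. The different working of the last-available rule for dropouts follows from the schedule itself and needs no such assumption. This is a cheap improvement worth making before enrolment, not a defect shown to invalidate the comparison.

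**What to change.** In Table 1 and section 2.9, replace the empty TAU assessments at weeks 4 and 8 with the same questionnaire pack and the same reminders as in HRTP: BDI-II, RTS and TSDS, plus HAq-II and RMCS if these are to be compared between arms at week 12. Bring the time points in section 2.12 into line, and reconcile section 2.10's restriction of HAq-II and RMCS to the treatment group with Table 1 and section 2.12.

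Completions of the primary scales at week 12 then become four against four. The schedule-induced difference is removed by design, dropouts in both arms can contribute interim scores, and the HRTP phase description is kept and gains a TAU comparator.

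Cost: at most 48 × 2 = 96 extra packs. At the pilot's $30 per battery (section 2.4, given there as an example and not as this trial's rate) that is 96 × $30 = $2,880 in payments, plus a small added burden for TAU participants. Equalising the other way, by taking the scales out of HRTP at weeks 4 and 8, is not advised, because it would give up the stated aim of describing change during treatment.

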### 2.10. Secondary Outcomes

Two secondary outcomes will also be measured at three time points within the treatment group only (weeks 4, 8, and 12). See Table 1 for the participants’ assessment schedule.

The *Helping Alliance Questionnaire* (HAq-II; Luborsky et al., 1996) is a 19-item clinical measure which asks respondents to consider their relationship with their therapist, and rate items according to how strongly they agree or disagree. Sample items include “I feel I am working together with my therapist in a joint effort” and “The therapist and I make unprofitable exchanges”. Items are rated on a 6-point scale, where “1” is strongly disagree and “6” is strongly agree. A total score is calculated from a sum of all items (with some items requiring reverse scoring first). Higher scores are indicative of a better-quality therapeutic alliance between the respondent and the therapist, as perceived by the respondent. The HAq-II has a test–retest reliability over a three-session span of 0.78. It has previously been tested with African American adult clients in a substance use treatment setting, finding comparable conceptualizations of the therapeutic alliance (Dillon, 2013).

The *Racial Microaggressions in Counselling Scale* (RMCS; Constantine, 2007) is a 10-item clinical measure designed to assess the occurrence of subtle covert expressions of prejudice or racism (i.e., microaggressions) within the therapeutic setting as perceived by the respondent/client. Sample items include “my counsellor avoided discussing or addressing cultural issues in our session(s)” and “my counsellor sometimes seemed unaware of the realities of race and racism”. Items are rated on a 3-point scale where “0” is this never happened and “2” this happened and I was bothered by it. An RMCS total is obtained by summing all item ratings together, with higher total scores suggestive of more microaggressions being observed within the therapeutic setting. The RMCS was developed for and tested within diverse ethnoracial groups.

